## Abstract

**Background:**

Oppositional Defiant Disorder (ODD) is characterized by angry and noncompliant behaviour. It is the most common disruptive behaviour disorder (DBD), with prevalence estimates of 6-9% for preschoolers and is closely linked to several long-term difficulties, including disorders of conduct, mood, anxiety, impulse-control, and substance abuse. ODD in children is related to parental depression, family dysfunction, and impairments in parental work performance. Children displaying early DBDs exhibit more symptoms of greater severity, more frequent offences, and commit more serious crimes later in life. The goal of the Strongest Families™ Finland Canada (SFFC) Smart Website intervention research program is to develop and evaluate an affordable, accessible, effective secondary prevention parent training program for disruptive behaviour in preschoolers to prevent the negative sequelae of ODD. Strongest Families is an 11-session program with two booster sessions that focuses on teaching skills to: strengthen parent–child relationships; reinforce positive behaviour; reduce conflict; manage daily transitions; plan for potentially problematic situations; promote emotional regulation and pro-social behaviour and decrease antisocial behaviour.

**Methods/design:**

This protocol paper describes an ongoing population-based randomized controlled trial (RCT) of high-risk 4 year-olds attending well-child clinics in Turku, Finland and environs to examine the effectiveness of the Strongest Families Smart Website intervention compared to an Education Control condition. Randomization consists of a 1:1 ratio for intervention versus the education group, stratified by the child’s sex. The participants randomized to the intervention group receive access to the Strongest Families Smart Website and weekly telephone coaching sessions. The participants randomized to the Education Control condition receive access to a static website with parenting tips. Children are followed using parental and daycare teacher measures at 6 and 12 months after randomization.

**Discussion:**

The Strongest Families Smart Website intervention is hypothesized to improve parenting skills, reduce child disruptive behaviour, reduce parental distress and improve family functioning. These results will likely inform subsequent investigations, public policy, and early treatment of childhood disruptive behaviour problems.

**Trial registration:**

ClinicalTrials.gov # NCT01750996

## Background

### Overview of childhood disruptive behaviour and parent training

Oppositional Defiant Disorder (ODD) [1] is the most common disruptive behaviour disorder (DBD) [2], with prevalence estimates of 6-9% for preschool children (with a higher percentage displaying symptoms that do not meet diagnostic criteria) [2,3]. ODD is characterized by angry/irritable mood, argumentative/defiant behaviour, and vindictiveness. Population-based birth cohort studies have shown that childhood psychiatric problems are developmental precursors for a wide range of negative outcomes indicating risk of marginalization including peer rejection, school failure, psychopathology, substance abuse and criminality [4], and the prognoses are often poor [5-14]. Approximately half of those children whom have been identified as aggressive with externalizing behaviour at preschool age eventually develop persistent problems [15,16] and there seems to be a developmental trajectory of early onset ODD that leads to Conduct Disorder (CD) in a proportion of these children [7]. In children, ODD has also been linked to parental depression [17,18], family dysfunction [18], and impairments in parental work performance [19].

Disruptive behaviour disorders such as ODD are among the most costly of early childhood psychiatric disorders [7]. In children aged 3–8 years, DBDs cause substantial annual costs [20]. Despite an established knowledge base, few strategies have been developed to prevent this trajectory at an early stage and at the population level.

Many parents react to defiant, oppositional behaviour with an increase in controlling strategies and a decrease in positive responses [17]. Forty years ago, Patterson and Reid described the mechanisms via which this coercive pattern contributes to an escalation in disruptive behaviour and more serious antisocial behaviour [21]. This pattern has been confirmed in longitudinal studies [17,18], and leads to diminishing emotional regulation and poor peer relationships [22-24]. Elgar and colleagues [24] examined 4,184 parents and 6,048 ten to fifteen year-old children and youth enrolled in the 1998 and 2000 cycles of the Canadian National Longitudinal Survey of Children and Youth (NLSCY), and found that parenting style predicted both internalizing and externalizing behaviour in children and youth. Although genetics can play a role in disruptive behaviour [25,26], an important implication of the research points to the possibility that early parenting interventions may have epigenetic effects [27,28] that alter the genetic contribution to child outcomes.

Parent training has been shown to be the most effective approach to the prevention and treatment of disruptive behaviour [29-32] and it represents one of the most well-validated therapeutic techniques [33]. The effectiveness of parent training has been established in small groups [34,35], large groups [36,37], and home-based coach-supported distance formats [38].

Parent training is a heterogeneous mode of treatment [39,40], differing in theoretical orientation, amount of intervention, qualifications of the training administrator, mode of delivery, therapeutic components provided, and targeted recipients (e.g., parent only or with the child receiving therapy). In parent training interventions, parents typically learn to identify, define and observe problem behaviours in new ways, as well as learn strategies to prevent and respond to oppositional behaviour [33]. A recent meta-analytic review of parenting programs found that the following program components were consistently related to larger effects: (1) increasing emotional communication skills and positive parent–child interactions, (2) teaching parents to utilize time-out and about the importance of consistent parenting, and (3) requiring practice of new skills between parents and children during parent training sessions [41].

Despite its promise, traditional parent training programs have significant limitations. In Finnish [42], Canadian [43], and American utilization studies [44], most (i.e., about 80%) children with externalizing problems do not receive timely treatment. Moreover, logistical barriers such as child care, transportation time, work schedules, stigma, or discomfort with services delivered in groups prevent many parents from enrolling in or completing parent training programs [39,45-50]. Lastly, low income, limited education, maternal stress, and parental depression [51], can interfere with program completion, limiting the effectiveness of currently available models for families at greatest risk.

The Finnish universal health care system, with its high participation rate in child check-ups and recent emphasis on psychosocial well-being of families (including parenting), represents an exceptional opportunity to study the outcome of parenting skills programs targeted to families with children who present with high levels of oppositional behaviour problems.

### The Strongest Families Finland Canada (SFFC) Smart Website Intervention Program

Based on the reviewed research, we concluded that an ideal intervention for disruptive behaviour problems should, (1) target behaviour problems emerging in the preschool years, (2) be effective, (3) be affordable enough to be implemented widely, (4) appeal to parents who do not use or have ready access to available, traditional programs, (5) be flexible enough to customize the intervention to meet the child’s and family’s needs, and (6) facilitate an integrated system that includes early identification at the population level and management of difficulties, with follow-up after intervention to maintain the effect.

### Study goals

The goal of the research program is to translate and replicate the Strongest Families™ telephone-based program in a Finnish population trial using a Smart Website delivery system. A population-based randomized controlled trial (RCT) is currently being conducted with 4 year-old children displaying disruptive behaviour. Specific objectives of the SFFC Smart Website intervention research program are to:

(1) develop a collaborative network that builds partnerships among investigators that will inform the content of our existing program by harnessing the advances of technology to customize care using videos, audio-clips and written exercises that demonstrate skill implementation;

(2) develop methods for early identification of challenging behaviour in primary health care in Finland;

(3) evaluate the prevalence of early signs of disruptive behaviour in Finnish 4 year-old children;

(4) develop the Strongest Families Smart Website intervention based on the Strongest Families telephone-based program [38] for the prevention and treatment of disruptive behaviour in 4 year-old children;

(5) evaluate the effectiveness of the Strongest Families Smart Website intervention for the early identification and treatment of disruptive behaviour in 4 year-old children, compared to an Education Control condition; and

(6) examine the possible moderating influence of program utilization using tracking reports of website activities (e.g., time on task, number of screens viewed, sessions completed).

### Study hypotheses

#### Primary hypothesis

The primary hypothesis of this study is that the Strongest Families Smart Website intervention will reduce child disruptive behaviour symptoms and impairment scores on the *The Child Behavior Checklist-Parent Report Form (CBCL) 1½–5 years* of the Achenbach System of Empirically Based Assessment (ASEBA) [52] after treatment and at one year follow-up, compared to the Education Control condition.

#### Secondary hypothesis

To supplement this primary hypothesis, it is also hypothesized that after treatment, and at one year follow-up, those participants randomized to the Strongest Families Smart Website intervention will exhibit improved scores on parenting style (*The Parenting Scale [PS]*) [53,54], parental distress (*Depression Anxiety and Stress Scale Short Form [DASS-21]*) [55], and teacher evaluation of school-related child behaviour scores *(The Child Behavior Checklist-Teacher Report Form [TRF]* of the Achenbach System of Empirically Based Assessment [ASEBA]) [52], compared to the participants randomized to the Education Control condition.

## Methods/design

### Design of the study

The study design is a two parallel group RCT stratified by sex, with 1:1 individual allocation comparing the Education Control condition and the Strongest Families Smart Website intervention (Intervention). Best practice guidelines for conducing RCTs will be followed in accordance with the CONsolidated standards of Reporting Trials statement (CONSORT), European International Conference on Harmonisation (ICH) Good Clinical Practice Guidelines, and Tri-Council Policy Statement: Ethical Conduct for Research Involving Humans (trial registry: ClinicalTrials.gov # NCT01750996).

#### Ethics

Our study protocol was approved by our Research Ethics Boards (i.e., Intermunicipal Hospital District of Southwest Finland Ethics Committee, IWK Health Centre Research Ethics). All data is collected with voluntary consent. The voluntary consent forms were formulated according to guidelines set by the Ethics Committee and they were approved in the process of the Ethics approval.

#### Screening and inclusion criteria

Inclusion criteria for the RCT are as follows: (1) the child meets the screening criteria (i.e., the age of 4 years); (2) native language of Finnish or Swedish for at least one of the parents; (3) residence in any of the participating municipalities; (4) in the screening phase, the child has had behavioural challenges for the last six months (score of 5 points or more on the Conduct subscale of the Strengths and Difficulties Questionnaire [SDQ] [56] and with some perceived problems by the parent in the impact section); (5) the parent has access to a telephone, computer, and an internet connection in their home (a computer with an internet connection is provided to families if needed); (6) and the ability of one of the parents to speak and read Finnish.

Participant recruitment began on October 1^st^, 2011 in Turku, Raisio, Kaarina and Naantali cities located in Southwestern Finland (total population of 254,974 at the end of 2012). On October 1^st^, 2012, seven smaller municipalities were enrolled in the study (total population of 76,915 at the end of 2012) [57].

The participants are selected from the Finnish National Population Register [58]. These participants are mailed a study information package approximately one month in advance of the four-year clinic visit. This package contains a brochure reminding the participants of the upcoming extended child health check-up, information about the study required by the Ethics Regulations, and a health questionnaire containing a Finnish translation of the SDQ [56]. The participants are asked to complete the health questionnaire and are encouraged to bring the completed questionnaire to the clinic. If the questionnaire is absent, the health nurses ask the participants to complete the questionnaire during the appointment. In the event that a participant is not interested in the study, the nurse notes “declined to participate”. All of the families of 4 year-old children attending the check-up receive a small token of appreciation from the study team (i.e., a children’s book). After the appointment, the health nurses mail the completed questionnaires to the study site, data is entered into a study database and the SDQ’s are scored.

Those participants with a child meeting the screening inclusion criteria are enrolled in the next phase of the study. The study staff complete a recruitment telephone call introducing the study in more detail and screening for eligibility. During this telephone call, if the participant expresses their preliminary interest in participation, they are registered in the Smart Website electronic platform called IRIS (Intelligent Research and Intervention Software). If the participant declines to participate or is ineligible for the study, a record of this is entered into the system. If recruitment is successful, the data submitted by study staff generates an automated email trigger from IRIS to the participant containing instructions to set up a password for IRIS. On first login, the participating parents are presented with the online consent form. A separate consent telephone call with the parents is scheduled a few days after the recruitment telephone call. During the consent telephone call, the staff confirms the parents’ online consent, and, if consent is provided, the online baseline measures in IRIS are released to be completed by the participating parent. Once the online baseline questionnaires are completed, IRIS sends a task prompt to the study staff to complete the randomization process.

#### Exclusion criteria

Exclusion criteria for the child are as follows: is not speaking in full sentences; is deaf or blind; has received or is receiving behavioural treatment (i.e., parent training); or has a diagnosis of Autism or a Pervasive Developmental Disorder (PDD), Down’s syndrome, Fetal Alcohol Syndrome, mental retardation, genetic diagnosis that will lead to mental retardation, or a major mental health disorder (e.g., depression, psychosis). Exclusionary criteria for parents include: current involvement with child protection services (i.e., removal of child custody, investigation of child abuse or neglect); child not living at home; a major mental health disorder, physical or other severe illness; and long-term hospital visits or care that would interfere with study participation. The exclusion criteria for the child and family are based on parent report during the recruitment call.

#### Sample size

As per Cohen’s [59] suggestion that standardized effect sizes of 0.20, 0.50 and 0.80 be considered as small (detectable), medium and large, respectively, we expect to observe medium to small incremental effects in the order of 0.30 to 0.35 standard units between the intervention and control groups, accounting for multiple comparisons using hierarchical linear modelling (HLM) analysis. This would require 250 participants per group for the trial, allowing for 30% attrition over time. It is expected that adding data from one year follow-up will increase the power to detect differences. An alpha of 0.05 was chosen on an *a priori* basis for the statistical analyses in order to decrease the probability of type II errors.

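### The sample size section says HLM accounts for multiple comparisons; HLM does not do that, and nothing stated supports a multiplicity allowance in the 250 per group

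*Protocol article*

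**What the plan says.** The Sample size section anticipates "effects in the order of 0.30 to 0.35 standard units between the intervention and control groups" and continues "accounting for multiple comparisons using hierarchical linear modelling (HLM) analysis. This would require 250 participants per group for the trial", with 30% attrition allowed for. It sets alpha at 0.05, chosen in advance as the "basis for the statistical analyses in order to decrease the probability of type II errors". It adds: "It is expected that adding data from one year follow-up will increase the power to detect differences". It gives no power, no sidedness, no number of comparisons, no adjusted alpha and no correlation between repeated measures.

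The Primary hypothesis section expects a reduction in CBCL scores "after treatment and at one year follow-up, compared to the Education Control condition", which makes two time points.

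The Statistical analyses section describes a growth-curve model of CBCL externalizing scores. Repeated measures within a child form Level 1, and differences in coefficients between arms form Level 2. It plans a comparison of trajectories and also a formal test with the intercept moved to the end of the trial. It describes no adjustment for multiple testing.

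**The concern.** The article attributes to HLM a property that the method does not have. A multilevel model accounts for the dependence among one child's scores, so that standard errors are right. It does not limit the chance of a false positive when more than one hypothesis is tested at 0.05.

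The phrase stands directly before the required sample size, so a reader will take it that the trial was sized with multiplicity covered. The rest of the section does not bear this out. The single alpha is 0.05, and the reason given for it, fewer type II errors, is a reason for not tightening alpha.

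Two things are at stake. If both primary time points are tested at 0.05 and either may be claimed, the familywise error exceeds 5%. If alpha is split to prevent that, power at the lower planned effect may fall below what readers assume.

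**Working it through.** **Inputs from the article.** d = 0.30 to 0.35 (SD = 1), alpha = 0.05, 1:1 allocation, attrition 30%, 250 per group, two time points in the primary hypothesis.

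**Assumed, not stated.** Two-sided test; power of 80% unless another value is shown; a simple comparison of two means at one visit.

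**1. Reproducing 250.** Completers per group: n = 2(z_alpha + z_power)²/d².
- d = 0.30, alpha 0.05, 80%: 2(1.960 + 0.842)²/0.30² = 174.4, so 175. Then 175/0.70 = 250 (unrounded 174.4/0.70 = 249.2).

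The figure is reproduced by one comparison with no multiplicity adjustment.

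**2. Bonferroni at d = 0.30 and 80% power.**
- Two tests (alpha 0.025): 2(2.241 + 0.842)²/0.30² = 211.2; 211.2/0.70 = about 302 per group (303 if completers are first rounded up to 212).
- Three tests (alpha 0.05/3): 232.7 completers; about 332 per group.

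No Bonferroni allowance fits in 250 at this effect and power.

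**3. Is the match in step 1 unique?** Power is not stated and the effect is a range, so other settings were tried.

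| d | alpha | power | completers | per group |
|---|---|---|---|---|
| 0.30 | 0.05 | 80% | 174.4 | 249.2 |
| 0.35 | 0.05 | 90% | 171.6 | 245 |
| 0.35 | 0.025 (two tests) | 85% | 175.4 | 250.6 |
| 0.35 | 0.05/3 (three tests) | 80% | 170.9 | 244 |

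The last two rows contain an adjustment and land on or near 250. The match in step 1 is therefore not unique.

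**4. What 175 completers per group deliver.** Normal approximation: power = Φ(d·√(175/2) − z_alpha), with d·√(175/2) = 2.806 at d = 0.30 and 3.274 at d = 0.35.

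| alpha | d = 0.30 | d = 0.35 |
|---|---|---|
| 0.05 | 80% | about 90% |
| 0.025, per visit | 71% | 85% |

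These hold without baseline adjustment. With a baseline correlation r (an assumption), the variance shrinks by 1 − r². At d = 0.30 and alpha 0.025, power is then 79% at r = 0.4, 84% at r = 0.5 and 90% at r = 0.6. The two-test requirement falls to 250 when 1 − r² = 250/302, that is, at r of about 0.41.

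**5. Familywise error if both visits are tested at 0.05 and either may be claimed.** With an assumed correlation of 0.5 to 0.7 between the two test statistics, the chance of at least one false positive is about 9% to 8%.

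**The case against.** The strongest reply is that the number does not show the absence of an adjustment. A reader might infer from step 1 that 250 simply is the unadjusted size and that no multiplicity allowance is in it. That inference is circular: the article gives no power, and 80% is picked because it reproduces 250. Settings inside the article's own effect range reach the same number with an adjustment (step 3). The planned analysis also uses repeated scores including baseline, and a moderate baseline correlation would absorb a two-test split. This part of the reply stands.

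It can also be said that the article never commits to splitting alpha. The primary analysis is one model with an end-of-trial test, and one-year data are presented as added power. If success at either visit sufficed at 0.025 each, the chance of at least one success at d = 0.30 would be about 82% to 85% (test correlation 0.7 to 0.5). So the 71% is power per visit, not the power of the trial under every rule. This stands too.

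Finally, the phrase may describe the handling of repeated measures in one model, and a condensed article may leave the number of comparisons and the adjustment rule to a fuller document. The second part is fair, and the absence of those details is not the point here. The first does not rescue the wording: a model for repeated measures is not an account of multiple comparisons. The alpha rationale sits awkwardly beside the claim, but it does not prove how 250 was obtained.

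**Conclusion.** The point holds in this form: the article says that HLM accounts for multiple comparisons, the model it describes does not do so, and nothing else stated supports a multiplicity allowance in the 250 per group. The allowance is unsupported; the figure itself does not disprove it.

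At the lower planned effect, with two-sided 0.05 and 80% power assumed, 250 covers exactly one unadjusted comparison, and two Bonferroni tests would need about 302. At d = 0.35, or with a baseline correlation of about 0.41 or more, an allowance for two tests could fit.

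There is no arithmetic error in 250 and no case here for a larger trial. The fault is a wrongly described design property. It should be corrected, but it ranks below the faults that must be fixed before the plan can stand. Confidence is moderate, because power and sidedness are inferred and the analysis model is simplified in the check.

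**What to change.** In the Sample size section:
- Delete the statement that HLM accounts for multiple comparisons. If handling of repeated measures was meant, say that.
- State the power and sidedness used. If they were 80% and two-sided, say that 250 per group (175 completers after 30% attrition) gives about 80% power at d = 0.30 and 90% at d = 0.35 for one comparison at 0.05, with no multiplicity allowance. If another calculation lies behind 250, give its inputs.
- Either name one decisive primary comparison (visit and test), or report power at the alpha actually used for two. At 0.025 that is about 71% (d = 0.30) and 85% (d = 0.35) per visit without baseline adjustment. If a higher figure is quoted on the strength of baseline scores, state the assumed correlation.

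The cost is a change of text only. Enrolment stays at 250 per group, and the stated position becomes slightly less favourable.
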